## Abstract

**Background:**

Otorhinolaryngology (ORL) surgery is common in children, but hospitalisation, surgery, and home care after discharge are stressful experiences for young patients and their family caregivers. Findings from literature highlight a lack of time in hospitals to support ORL surgery children and their caregivers through the perioperative process, along with the risks of caregivers’ autonomous web or social media resources investigation. Therefore, this study aims to evaluate the effectiveness of a mobile health application with content to support ORL patients and their caregivers in the perioperative period to reduce caregiver anxiety and child distress compared to standard care.

**Methods:**

An open-label, two-arm randomised control trial design is being adopted. The intervention consists of a mobile health application with content to support ORL patients and their caregivers during the perioperative period. One hundred eighty participants will be enrolled and randomly assigned to the experimental group using the mHealth application or the control group. The control group receives standard information and education about the ORL perioperative period from healthcare providers orally or through brochures. The primary outcome is the difference between the intervention and control groups in preoperative caregiver state anxiety. Secondary outcome measures include children’s distress before surgery and family preparation for hospitalisation.

**Discussion:**

The results of this study will be critical to the implementation of a new and safe model for the management of care and education in paediatrics. This model can achieve positive organisational and health outcomes by supporting continuity of care and empowering citizens to have informed participation and satisfaction in paediatric health promotion and management.

**Trial registration:**

Trial identifier: NCT05460689 registry name: ClinicalTrials.gov. Date of registration: July 15, 2022. Last update posted: February 23, 2023.

## Administrative information

Note: the numbers in curly brackets in this protocol refer to SPIRIT checklist item numbers. The order of the items has been modified to group similar items (see http://www.equator-network.org/reporting-guidelines/spirit-2013-statement-defining-standard-protocol-items-for-clinical-trials/).

## Introduction

### Background and rationale {6a}

Tonsillectomy and/or adenoidectomy with or without insertion of a tympanostomy tube are common surgeries in children. However, authors report children and their family are distressed by these perioperative processes. Fear of the unknown may challenge the preoperative period, while pain and other possible complications such as fever, vomiting, limited oral intake, or bleeding may complicate the postoperative management at home [1, 2]. Moreover, parental anxiety has been found to worsen children’s perceptions of pain, perioperative distress, and recovery [3].

Preparing children and families for hospitalisation, surgery, and postoperative management at home has been shown to improve perioperative outcomes [2]. However, not all individuals understand and can benefit from the information provided by healthcarers. In fact, higher levels of anxiety in the perioperative process have been associated with individuals with low health literacy [4]. According to Sørensen and colleagues [5], “Health literacy is linked to literacy and entails people’s knowledge, motivation and competences to access, understand, appraise, and apply health information in order to make judgements and take decisions in everyday life concerning healthcare, disease prevention and health promotion to maintain or improve quality of life during the life course”. In paediatric surgery, this specifically includes the ability of parents or other caregivers to understand the rationale for surgery to treat their child’s condition, consent forms, preoperative and postoperative instructions, and/or drugs prescriptions. Low health literacy in paediatrics has also been found to affect health-related outcomes and child safety, as well as with preventable hospitalisations [6]. Therefore, authors advocate the health literacy benefits of a family-centred perioperative care and education. The information needs of children and their caregivers, their health literacy, learning and coping styles, and the family’s experiences in the hospital, such as with invasive or painful procedures, are all factors to consider in this process for each family unit [4, 7]. However, patient- and family-centred education and support is a complex and time-consuming care interventions, whereas some surgical procedures, such as tonsillectomy, are characterised by a short hospital stay, thus limiting the time that healthcare providers can devote to this program [8]. Moreover, unmet information needs may lead parents or other caregivers to expose themselves to health-related misinformation through autonomous web and common social media resources investigation [9, 10]. Therefore, health systems have tested different types of formats, content, and delivery of education to meet client needs, time availability, and effectiveness. A systematic review that aimed at exploring the types and benefits of patient/parent education programs prior to tonsillectomy identified several educational methods for tonsillectomy management, such as verbal information for caregivers, informational brochures, videos, Internet resources, mobile health applications (mHealth apps), and mobile reminder text messages. In particular, mHealth apps and text messaging were consistently shown to be beneficial to patients in terms of pain, stress and compliance, and the authors recommend their use in clinical settings where other types of perioperative education are lacking or do not lead to positive outcomes [2, 11].

In particular, mHealth apps are an essential element of electronic health and consist of medical information available through mobile phones or other wireless devices that can be used by patients or healthcarers. Their use is increasing and evolving in a variety of functions and positive outcomes related to the improving the well-being of individuals, including diagnostics and clinical decision making, healthy lifestyles interventions, disease management, and self-care [12]. However, findings from literature reviews addressing current research on the use of clinical apps indicate that further randomised controlled trials with larger sample size (> 60) and improved rigour in study design and methods are needed to confirm positive outcomes [13, 14]. Moreover, in a literature review of qualitative studies exploring patients’ perceptions of mHealth apps, results reported customer satisfaction and engagement in their own care through the use of apps. However, weaknesses of mHealth apps have also been reported, including lack of disease-specific, cultural, and health literacy level personalisation, accessibility, and evidence-based information [15]. Furthermore, to our knowledge, there are few studies testing mHealth apps for family-centred perioperative tonsillectomy and/or adenoidectomy with or without tympanostomy tube insertion.

Therefore, this study aims to investigate the effectiveness of an mHealth app in supporting caregivers of children undergoing tonsillectomy and/or adenoidectomy, with or without insertion of a tympanostomy tube, in a family-centred and health literacy-focused manner in an Italian maternal and child health hospital compared to standard care. Moreover, objective of this study is also to evaluate the impact of the app on the surgical ward and other organisational aspects of the hospital compared to standard processes.

### Objectives {7}

Based on these premises, the following research questions will be addressed:Does an mHealth app designed to support caregivers of children undergoing tonsillectomy and/or adenoidectomy with or without tympanostomy tube insertion in the perioperative process improve family-health related outcomes compared to standard care?Does an mHealth app designed to support caregivers of children undergoing tonsillectomy and/or adenoidectomy with or without insertion of a tympanostomy tube improve organisational issues of the surgical ward in the perioperative process compared to standard care?

Therefore, the primary objective of the study is to determine the effectiveness of a plain-language mHealth app compared with other standard supportive and educational methods on anxiety of caregivers of children undergoing tonsillectomy and/or adenoidectomy with or without insertion of a tympanostomy tube.

Secondary objectives are to determine the effectiveness of a plain language mHealth app compared with other standard supportive and educational methods in terms of family preparation for hospitalisation and surgery, child distress, family satisfaction with care, and post-discharge management at home.

### Trial design {8}

A two-parallel arm, open randomised controlled trial is being conducted to evaluate the superiority of an mHealth app in reducing anxiety in caregivers of children undergoing tonsillectomy and/or adenoidectomy with or without insertion of a tympanostomy tube in the perioperative period compared to standard care. Standard care in the control group consists of information and education provided by nurses and physicians during preoperative visits and hospitalisation about the ORL perioperative process. The information and education are provided orally or through printed brochures. Eligible participants are randomly allocated in a 1:1 ratio to the intervention group (use of mHealth app) or the control group (standard care).

Our study protocol followed the SPIRIT guidelines [16].

## Methods: participants, interventions, and outcomes

### Study setting {9}

The study is monocentric and is being conducted in a 136-bed maternal and child health hospital in Northern Italy. In this hospital, a number of approximately 450 tonsillectomies or adeno-tonsillectomies are performed each year. Specifically, enrolment started December 16, 2022, and is taking place in the consulting rooms of the paediatric surgery ORL department. Data collection is being performed in the paediatric surgery ward and in the ORL department. Statistical data analysis will be held at the clinical epidemiology and public health research unit of the same hospital.

### Eligibility criteria {10}

The inclusion criteria are as follows: (1) caregivers of male and female children aged at least 2 years and no more than 10 years who are scheduled for tonsillectomy and/or adenoidectomy with or without insertion of a tympanostomy tube, (2) caregivers who are capable of oral and written Italian communication without impairment, and (3) caregivers who guarantee access to a smartphone and Internet connection. The exclusion criteria will be as follows: (1) caregivers with cognitive impairment,,(2) caregivers of children with cognitive impairment, (3) caregivers with visual impairment, (4) caregivers of children affected by chronic pain, (5) caregivers of children who had another surgical procedure in the previous month, and (6) caregivers who have never used at least one smartphone app.

### Who will take informed consent? {26a}

Nursing staff in the consultation rooms of the paediatric surgery ORL department are in charge of informing eligible caregivers about the study and obtaining signed informed consent from caregivers to voluntarily participate in the study.

### Additional consent provisions for collection and use of participant data and biological specimens {26b}

The present study does not involve the collection or derivation of data and biological specimen for purposes that are separate from the main trial.

## Interventions

### Explanation for the choice of comparators {6b}

Standard care was chosen as comparator. Standard care given to caregivers in the ORL perioperative process consists of information and education provided by nurses and physicians during preoperative visits and hospitalisation about the ORL perioperative process. Standard information and education include topics such as ORL surgical and anaesthesiologic techniques that will be performed or strategies for pain control at home after surgery. Information and education is usually provided orally and through printed brochures.

### Intervention description {11a}

The intervention group (group A) uses an a mHealth app for information and education to caregivers of children undergoing tonsillectomy and/or adenoidectomy with or without insertion of a tympanostomy tube in the perioperative process. Group A has the app in use from the day of enrolment to the day of follow-up visit. Group B receives standard care.

The content and functions of the mHealth app were developed in collaboration with an institute of maternal and child health and Area Science Park, both in Northeastern Italy. The methodological steps followed to develop the mHealth app were guided by the three cycles of the Information System Research Framework [17]. The mHealth app was developed using a user-centred participatory design approach that involved both caregivers of ORL surgical children (primary users) and hospital staff (secondary users) to understand their needs and expectations related to content topics and functionalities [18]. To promote an equally accessible understanding of the mHealth app content, a team of external communication experts was also consulted, and content, such as terminology, was simplified where necessary.

The information and education content provided in standard care to the control group by healthcare providers during hospital visits, either orally or in the form of brochures are similar to that provided to the intervention group through the medium of the mHealth app. Information topics included, for example, explaining of the surgical procedure chosen, the type of anaesthesia used, strategies for preparing children for hospitalisation and surgery, or how to manage pain at home after discharge. Because healthcare providers have little time available to inform the family about safe surgery and other topics due to the short hospital stay that characterises this type of surgery [8], the content in the app is expanded and caregivers have the opportunity to read it at the time that best suits them and with the time they need. In fact, all content is available to users at any time in a library section of the app. Moreover, in accordance with the principles of adult learning [19] and its application in telemedicine [20], the content of the application is adapted to the needs of the primary end-users and delivered “just in time” [20]. In particular, content is suggested to participants in the form of new content notifications that are available based on the specific perioperative period the child is in, such as the day of prehospital visits, the prehospital period, the day of hospitalisation and surgery, and the post-discharge period at home. Moreover, pop-up messages are displayed to the user as reminders of visits or documents to bring to the hospital. All the content is provided in text format and in Italian. This mHealth app has the potential to enable communication between primary and secondary end-users, but these features are not used by study participants and are not the subject of this study experiment.

The nurses from the ORL paediatric surgical department are in charge of caregivers of ORL surgical children enrolment. These nurses, who are familiar with all the content, functions and features of the mHealth app, are also responsible for instructing group A participants on (1) how to download the app to their smartphone or tablet and (2) how to use the mHealth app and what functions and content it offers. The app developers also created a three-minute presentation of the mHealth app, which is shown by the nurses on a tablet to the group A participants after enrolment. The mHealth app is available for group A from the day of the pre-surgery visit until the seventh day after surgery or follow-up, which usually totals 14 days. The iOS and Android app provided to group A complies with technical and sectoral regulations such as the GDPR and the NIS directive, meets standards such as ISO/IEC 27,001 and the CE label, and consists of the following: a web-based platform with a modular architecture for information support and dialogue with users, certified according to DM 93/42/CE in the class II A and meets the main sectoral requirements for functional and reliability. Moreover, the app platform and all related services are developed in accordance with the rules of the Three-Year Plan for Information Technology for Public Administration (2019/2021), as far as they are compatible, and in accordance to the “Cloud First” principle.

The app is available free of charge and is available to the hospital’s end-users. However, until the end of the trial, the app will only be available to group A study participants.

### Criteria for discontinuing or modifying allocated interventions {11b}

In the event of a child’s fever or other issues causing a delay in surgery, the possibility to use the app and its content in the correct time frames will be adjusted to reflect the new surgery date selected.

### Strategies to improve adherence to interventions {11c}

Considering the functionality of the app, for example, allowing content to be delivered “just in time” [20] and depending on the specific perioperative period and potential needs of the user, not only is caregiver education made more effective but also their interest in continuing to use the app is stimulated. In addition, pop-up notifications and reminders from the app assist group A participants in using the app and reading its content. Moreover, groups A and B participants are encouraged to attend scheduled visits where healthcare providers give ORL perioperative information and education.

### Relevant concomitant care permitted or prohibited during the trial {11d}

We consider and permit that participants of group A and B may be exposed during the study to information derived from consultation of other health care experts, books, or web and social media.

### Provisions for post-trial care {30}

If this study demonstrates evidence of the effectiveness of the mHealth app, the app will be available for free download and use by caregivers of children undergoing tonsillectomy and/or adenoidectomy at this hospital, with or without the insertion of a tympanostomy tube.

### Outcomes {12}

The primary outcome of the study is the difference between the intervention and control groups in terms of caregivers’ self-reported state anxiety. It is be measured using the State-Trait Anxiety Inventory form Y questionnaire [21] in the surgical department, before the caregiver and child go into the operating theatre on the day of surgery, approximately seven days after enrolment.

Secondary outcomes are:The difference between the intervention and control groups in caregiver preparation for hospitalisation and surgery, evaluated at arrival at the hospital using a checklist completed by the administrative nurse (e.g. number of documents missing on arrival) approximately 5 days after enrolment;The difference between the intervention and control groups in preparing children for surgery, evaluated by ORL surgical nurses on arrival at the surgical department, approximately 5 days after enrolment;The difference between the intervention and control groups in terms of children’s distress. It is assessed by ORL surgical nurses in the surgical department using the modified Yale Preoperative Anxiety Scale [22];The difference between the intervention and control groups in self-reported primary caregiver anxiety as measured by the State-Trait Anxiety Inventory form Y questionnaire [21] on the day of follow-up, around the seventh day after surgery and 13 days after enrolment.The difference between the intervention and control groups in terms of the social and health effects of the introduction of an mHealth app in a maternal and child hospital. It is evaluated on the day of follow-up, approximately 14 days after enrolment.

### Participant timeline {13}

Caregivers participate in the study from the day of enrolment to day 7 after surgery or follow-up. The assessment time points (T) for caregivers and children after enrolment and signing of the informed consent form are as follows:(T0) after enrolment and allocation, data collection at time zero—(a) demographic data and (b) caregiver anxiety trait and state; (c) caregiver health literacy. At T0, participants in group A receive the app (intervention), while group B continue to receive standard care;(T1) at hospital admission on the day of surgery—IRCCS administrative office (“Punto benvenuto”)—documents required for hospital admission and surgery;(T2) upon admission to the surgical department ORL—(a) caregiver’s state anxiety level; (b) child’s preparation for surgery; (c) child distress;(T3) at follow-up—caregiver’s state anxiety; social impact.

Participant timeline is shown schematically in Fig. 1.

**Fig. 1 Fig1:**
[figure not shown]
Timeline schedule of enrolment, interventions, and assessments

### Sample size {14}

Assuming a mean score of preoperative anxiety (main outcome of the study) of 50 for the control group, with a standard deviation (SD) of 13 [21], and a mean of 45 for the intervention group, with SD of 10 (effect size = 0.43), an alpha value of 0.05 and a beta value of 0.20, 180 subjects (90 per group) are needed to conduct the study (G*power, Wilcoxon-Mann–Whitney test, two groups).

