### Recruitment {15}

Caregivers of children selected for ORL surgery and accessing the hospital are screened according to inclusion and exclusion criteria. The caregivers are offered to participate in this study. Recruitment is expected to last 8 months and will continue until the estimated sample size is reached.

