### Methods in analysis to handle protocol non-adherence and any statistical methods to handle missing data {20c}

The main analysis is performed as “intention to treat.” All randomised subjects with an available main outcome will be analysed in the group to which they were randomised, regardless of whether they received the assigned intervention. Reasons for dropping out of the study are recorded in a data file and described in detail. A multiple imputation technique will be used for missing data.

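### The 180 caregivers to be enrolled are exactly the 180 who must be analysed for 80% power, so the stated power leaves essentially no allowance for a missing T2 score.

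*Protocol article*

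**What the plan says.** All references are to the protocol article.

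- **Sample size {14}**: the inputs are a control mean of 50 (SD 13) and "a mean of 45 for the intervention group, with SD of 10 (effect size = 0.43"). The type I error is 0.05 and beta is 0.20. The calculation is for the Wilcoxon-Mann-Whitney test in G*Power. It concludes that "180 subjects (90 per group) are needed to conduct the study".
- **Abstract, Methods**: "One hundred eighty participants will be enrolled and randomly assigned to the experimental group" or to control.
- **Recruitment {15}**: recruitment "will continue until the estimated sample size is reached".
- **Section {20c}** (non-adherence and missing data): "All randomised subjects with an available main outcome will be analysed" in their randomised group. Reasons for dropping out are to be recorded. The section ends by promising multiple imputation for missing data, without saying for which variables or which analysis.
- **Statistical methods {20a}**: the primary test is Wilcoxon-Mann-Whitney, with a t-test as the alternative where needed.
- **Outcomes {12} and Participant timeline {13}**: the primary outcome is state anxiety at T2, in the surgical department on the day of surgery, about seven days after enrolment. State anxiety is also measured at T0, which the timeline places after allocation.

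**The concern.** Three stated quantities do not fit together. The number needed is 180 and the number randomised is 180, but the number analysed is 180 minus those without a T2 score. A caregiver can be randomised at the pre-surgery visit and still have no T2 score if the operation is cancelled, if the caregiver withdraws, or if the form is not completed before theatre. No section adds an allowance for this.

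The stated beta of 0.20 then describes a trial with complete primary data, not the trial that the analysis rule will produce. A null result could be reported as coming from an 80%-power trial when the analysed set gave somewhat less.

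**Working it through.** **Inputs.** Means 50 and 45, SDs 13 and 10, alpha 0.05, power 0.80, Wilcoxon-Mann-Whitney (all Sample size {14}); 1:1 allocation (Trial design {8}). The section does not say whether alpha is one- or two-sided.

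**Step 1: effect size.** d = 5 / √((13² + 10²)/2) = 5 / √134.5 = 5 / 11.597 = 0.431, which matches the printed 0.43.

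**Step 2: reproduce the 180.** Power is taken from the noncentral t distribution. The arm size is multiplied by the Wilcoxon test's asymptotic relative efficiency under normality, 3/π = 0.955:

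- effective n per arm = 90 × 0.955 = 85.9
- noncentrality = 0.43 × √(85.9/2) = 2.82
- two-sided power = 80.0% (80.2% at d = 0.431)

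At 89 per arm, power is 79.6% (79.8% at d = 0.431), so 90 is the smallest equal arm size that reaches 80%. A simulation with N(50, 13) and N(45, 10), 90 per arm and 20,000 runs gave 79.8%.

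Other variants give different totals: two-sided t-test 172, one-sided Wilcoxon 142, two-sided Wilcoxon with minimum efficiency 0.864, 198 to 200. Of these, only the two-sided Wilcoxon under normality gives 180, and it contains no dropout inflation.

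**Step 3: power if 180 are enrolled and some lack T2.** The loss rates are assumptions, because the article gives none. Figures are at d = 0.431; at 0.43 each is about 0.2 points lower.

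| Missing T2 | Analysed | Wilcoxon | t-test |
|---|---|---|---|
| 0% | 180 | 80.2% | 82.0% |
| 5% | 171 | 78.2% | 80.0% |
| 10% | 162 | 75.9% | 77.9% |

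Higher rates look unlikely for a measure taken in hospital about a week after enrolment. For completeness, Wilcoxon power is 73.5% at 15% and 70.9% at 20%.

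**Step 4: what imputation could recover.** As a rough assumption, imputing from a baseline correlated r with the outcome recovers a share r² of the missing information. With 10% missing and r = 0.5, the effective loss is 10% × (1 − 0.25) = 7.5%, and Wilcoxon power is about 77%. That is a partial recovery.

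**Step 5: what baseline adjustment could recover.** ANCOVA on T0 state anxiety shrinks the residual SD by √(1 − r²), so the effect becomes 0.431 / √(1 − r²). At 162 analysed (81 per arm):

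| Assumed T0–T2 correlation r | Adjusted effect | Power |
|---|---|---|
| 0.1 | 0.433 | 78% |
| 0.2 | 0.440 | 79% |
| 0.3 | 0.452 | 82% |
| 0.5 | 0.498 | 88% |

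Part of the gain over the Wilcoxon figure of 75.9% comes from moving to a t-type test, which alone gives 77.9% at 81 per arm. The correlation is not in the article.

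**The case against.** The case against has four parts, and most of it stands as a limit on size.

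**Imputation.** A reader might infer from section {20c} that missing outcomes are simply dropped. The text does not support that, because the same section promises multiple imputation. However, it does not say that the imputation covers the primary outcome, and the analysis-set sentence points the other way. Step 4 shows that imputation would not restore the full 80% in any case.

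**The t-test option.** A reader might infer that 80% power requires every one of the 180 scores. Under the t-test allowed in section {20a}, 172 analysed suffice, so 180 − 172 = 8 losses (4.4%) could be absorbed. Even with the Wilcoxon test at the unrounded effect size, one missing score still leaves 80.0%. But the trial was sized on the Wilcoxon test, {20a} names it first, and the t-test also falls below 80% at 10% loss.

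**Loss is probably small.** T2 is completed on a tablet in hospital about a week after enrolment. A reader might count postponed surgery as a loss, but section {11b} adjusts the app's time frames to the new surgery date, and T2 is taken at admission for surgery, so a postponed case can still supply the score. The assessment more exposed to loss is T3, collected through an emailed link, and it is not primary. Section {20c} provides for recording drop-outs but predicts no rate.

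**Baseline adjustment is not a guaranteed remedy.** Its gain depends on an assumed correlation and falls just short of 80% at r = 0.2 with 10% missing. It also changes the primary test. And T0 is taken after allocation in an open-label trial, so knowing the arm could affect the T0 score. This is why the order of T0 and disclosure belongs in the fix.

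**Conclusion.** The concern holds in limited form. The sample size arithmetic is correct. The fault is that a number which must be analysed is used as the number to be enrolled, while the main analysis is limited to those with the outcome. The stated 80% therefore has essentially no allowance for missing T2 scores.

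The likely cost is a few percentage points: about 2 at 5% missing and about 4 at 10% with the Wilcoxon test, and less with the t-test. These sizes rest on assumed loss rates, the article's own means and SDs, two-sided alpha of 0.05 and approximate normality. The documents do not support a claim that the trial is seriously underpowered. It is worth correcting because correcting the stated power is cheap and because it affects how a null result would be read.

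**What to change.** No extra enrolment is needed. For scale, keeping 180 analysed would take 180/0.95, or 190, enrolled at 5% loss and 180/0.90 = 200 at 10%.

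1. **Sample size {14}**: state that 80% applies to 180 analysed with the two-sided Wilcoxon test. Give the expected number with T2 scores and the power at that number, for example about 76% at 162.
2. **Section {20c}**: reconcile the available-outcome analysis set with the imputation sentence. Say whether the primary outcome is imputed, and which analysis is the main one.
3. **Statistical methods {20a}**: make the primary comparison an ANCOVA of T2 state anxiety on arm and T0 state anxiety. Report its power over a range of correlations, labelled as assumptions.
4. **Participant timeline {13}**: have T0 completed before the allocation is disclosed.

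Items 1 and 2 are wording, and the stated power becomes slightly less favourable. Item 3 changes the primary test, so it needs an amendment and should be fixed before outcomes are compared by arm. Item 4 changes the order of steps at the enrolment visit and adds no data collection. Recruitment has already started, so item 4 can apply only to caregivers not yet enrolled, and the amendment should say how many had T0 taken after disclosure.
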